### Sample size and justification

The sample size was calculated using Raosoft® calculator [35] with Confidence level of 95% ± 5% and response distribution of (50%) to know the minimum sample size. The total sample size came out to be 14 per arm. The sample size of this study is equal to 15 per arm to obtain the statistical power for the study.

This calculation was based on a previous pectin pilot study which found significant differences in 4 inflammatory markers with n=14 healthy adult volunteers [31].

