A recent study by our group at University of Nottingham showed that 4 weeks consumption of a daily supplement containing 15-20g of LM pectin significantly reduced pro-inflammatory blood markers such as TNFα (p<0.003), increased anti-inflammatory blood marker IL-10 (p=0.08), decreased TLR-2 concentration in the blood (p<0.027) and improved gut permeability with no recorded side effects in healthy volunteers [31].

- Short-Chain Fatty Acids (SCFAs) production

As mentioned above, butyrate, one of SCFAs that is produced after LM pectin fermentation in the gut, may help reduce inflammation by influencing regulatory T cells in the gut lining that Can lead to increase the level anti-inflammatory cytokines like IL-10 [14]. This might reduce the systematic inflammation.

The diagram below summarises the effects of LM pectin on gut microbiota composition and systematic inflammation pathways in individuals with MASLD:

[figure not shown]

*Study aims*

Therefore, the current research aims to study the effects of LM pectin, the dietary supplementation intervention, on pathways contributing to systematic inflammation in patients with MASLD.

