### Assessment of efficacy

### Primary endpoint

Levels of serum inflammatory biomarkers such as; IL-6, IL-10, C-RP, Zonulin (Haptoglobulin), IL-1β, TNFα, IFNᵧ.

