### Secondary endpoint

- Change in BMI
- Change in general metabolic indicators such as fasting blood glucose
- Changes in blood-based markers relevant to MASLD (e.g., CK18-M30, CK18-M65, PROC3, Enhanced Liver Fibrosis (ELF), NIS2+™, YKL-40, microRNA miR-34a-5p, liver-associated enzymes such as Alanine Aminotransferase (ALT), Aspartate Aminotransferase (AST), gamma-glutamyl transferase (GGT), Alkaline Phosphatase (ALP)), bilirubin levels, lipid profiles, and platelet counts.
- Gut microbiome: changes in composition
- Change in non-invasive physiological assessments linked to liver characteristics: FibroScan™ CAP value and Liver stiffness based on vibration-controlled transient elastography (VCTE)
- Change in liver fat and other surrounding abdominal organs fat through alterations in Dixon MRI sequence
- Alterations in T2* MRI measures of intestinal permeability

The efficacy parameters for the primary and secondary endpoints will involve calculating the difference between baseline visit and follow-up visit in both study arms and compare between two arms. Moreover, they will be used in calculating correlation coefficients (Pearson's or other appropriate methods) between the effect of pectin compared to placebo, adjusting for baseline values and relevant covariates such as age, sex, ethnicity and BMI. These correlation coefficients will indicate the strength and direction of the relationships between the variables.

Primary endpoint has been identified based on the results on a recent study that was conducted at University of Nottingham, showed that 4 weeks ingestion of 15-20g/day of LM pectin in healthy volunteers significantly reduced pro-inflammatory blood markers [31].

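### The 14 (then 15) per arm comes from a precision calculation for one proportion, which cannot size a two-arm biomarker comparison, so the claim of statistical power is unsupported

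*Protocol*

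**What the plan says.** The Protocol, under Sample size and justification, names the tool and its inputs: "The sample size was calculated using Raosoft® calculator [35] with Confidence level of 95% ± 5% and response distribution of (50" per cent). It then reports "The total sample size came out to be 14 per arm" and concludes "The sample size of this study is equal to 15 per arm to obtain the statistical power for the study". The empirical support offered is: "This calculation was based on a previous pectin pilot study which found significant differences in 4 inflammatory markers with n=14 healthy adult volunteers". The Synopsis repeats the same text under Sample size estimate.

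The quantity to be compared is set out under Assessment of efficacy. The primary endpoint is "Levels of serum inflammatory biomarkers such as; IL-6, IL-10, C-RP, Zonulin (Haptoglobulin), IL-1β, TNFα, IFNᵧ", and the analysis involves "calculating the difference between baseline visit and follow-up visit in both study arms and compare between two arms". The Synopsis sets 0.05 as the significance threshold for every analysis. No target power, target difference, SD, dropout rate or multiplicity allowance is given.

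**The concern.** Confidence level, margin of error and response distribution are the inputs of a survey calculation: how many respondents are needed to estimate one percentage to within a stated margin. This trial estimates no percentage as its primary endpoint; it compares continuous markers between pectin and placebo. A size for that comparison needs a target difference, an SD, a significance level and a power, and the quoted calculation supplies none of the first, second or fourth.

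The Protocol nevertheless says that 15 per arm secures power. A reader of the eventual report could then take a non-significant result as coming from a trial shown to be able to detect the effect. It has not been shown to be able to do so.

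**Working it through.** **Inputs from the Protocol.** Confidence 95% (z = 1.96); ±5%, read as the margin of error E = 0.05; response distribution p = 0.5; stated result 14 per arm; planned size 15 per arm; significance threshold 0.05. Sidedness is not stated and is taken as two-sided.

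**Step 1: the Protocol's own figure.** The precision formula for one proportion in a large population is n = z²p(1−p)/E².

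- z²p(1−p) = 1.96² × 0.25 = 0.9604
- n = 0.9604 / 0.0025 = 384.2, so 385

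The stated 14 does not reproduce. Conversely, with n = 14 the margin for a 50% proportion is 1.96 × √(0.25/14) = 0.26, that is ±26 points rather than ±5.

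**Step 2: what would return 14.** With a finite population of size N the formula is n = N × 0.9604 / ((N−1) × 0.0025 + 0.9604).

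| N entered (none is stated) | n | Rounded up |
|---|---|---|
| 14 (the pilot's size) | 13.4456 / 0.9929 = 13.5 | 14 |
| 15 (one arm) | 14.406 / 0.9954 = 14.5 | 15 |
| 30 (both arms) | 28.812 / 1.0329 = 27.9 | 28 in total, 14 per arm |
| 45 (all participants) | 40.4 | 41 |
| 1,000 | 277.7 | 278 |

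A result of 14 per arm requires a population barely larger than the sample, so the answer largely repeats the number put in. Which population was entered cannot be known from the Protocol.

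**Step 3: what 15 per arm delivers.** For two independent groups of n = 15, power comes from the noncentral t distribution with 28 degrees of freedom and noncentrality d × √(15/2), where d is the between-arm difference in SDs of the quantity compared. The assumptions are two-sided alpha 0.05, complete data on 15 per arm and, unless stated otherwise, one marker.

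| Quantity | Result |
|---|---|
| d for 80% power | 1.06 |
| d for 90% power | 1.23 |
| Power at d = 0.5 | 26% |
| Power at d = 0.8 | 56% |
| Power at d = 1.0 | 75% |
| d for 80% power, alpha 0.05/7 = 0.00714 (seven markers, no baseline adjustment) | 1.38 |

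- **Baseline adjustment.** The detectable difference is multiplied by √(1−r²), where r is the correlation between baseline and follow-up. The Protocol gives no r. Assuming r = 0.5: 1.06 × √0.75 = 0.92 SD. Assuming r = 0.7: 1.06 × √0.51 = 0.76 SD. Here the SD is that of the follow-up value within arm.
- **Confidence interval.** The half-width of the 95% interval for the unadjusted difference is 2.048 × √(2/15) = 2.048 × 0.365 = 0.75 SD.

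**The case against.** The best defence is that the trial's stated purpose is to explore, that it forms part of a PhD project, and that the defect lies in the justification, not in the number, the allocation or the analysis. That is fair as far as it goes. Nothing here shows that 15 per arm is wrong: for one marker, complete data and a true difference of about 1.06 SD or more, it gives at least 80% power. But the Protocol does not say that the size was chosen for exploration. It makes a positive claim about power, and a later statistical analysis plan would leave that claim standing.

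Three stronger readings are tempting, and the Protocol does not support them.

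- **That 14 is simply the pilot's sample size fed in and returned.** N = 14 does give 14, but N = 30 gives 28 in total, which is also 14 per arm. The population entered is not stated, so the origin of 14 stays open.
- **That the four significant pilot markers are contradicted by the Project Rationale.** That section says the pilot "significantly reduced pro-inflammatory blood markers such as TNFα (p<0.003), increased anti-inflammatory blood marker IL-10 (p=0.08"), and adds a result for TLR-2 (p<0.027). IL-10 does miss the 0.05 threshold. However, the pro-inflammatory markers are introduced as examples, so the list need not be complete and does not refute a count of four.
- **That the pilot's p-values reveal this trial's power.** If they came from a before/after test in 14 people, they would translate into 73%, 42% and 27% here. If they came from a comparison of two groups of 14, the figures would be 90%, 65% and 44%. The Protocol does not say which test produced them, two of the three are given only as upper bounds, and the volunteers were healthy. No power figure should be taken from them.

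**Conclusion.** The point holds. The Protocol's only sample-size calculation is of a kind that cannot size this comparison, its stated inputs give 385 rather than 14, and the claim that 15 per arm secures power has nothing behind it.

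In size, 15 per arm has 80% power for about 1.06 SD on a single marker, and differences of 0.5 to 0.8 SD would be missed in roughly 74% to 44% of such trials. This rests on two-sided alpha 0.05, 15 completers per arm and no baseline adjustment. Adjustment would improve the figures by an amount that depends on an unknown correlation; splitting alpha over seven markers would worsen them to about 1.38 SD. Completeness is itself an assumption, because the withdrawal section promises only an attempt to replace participants who leave.

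A reader might infer that the trial is too small. That does not follow, because the Protocol names no target difference against which to judge it.

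**What to change.** In both the Synopsis and Sample size and justification, delete the survey calculation and the power wording, and replace them with text along these lines:

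> Fifteen participants per arm were chosen because [sponsor to give the true basis, for example feasibility if that is so]. With two-sided alpha 0.05 and 15 completers per arm, this gives 80% power for a between-arm difference of about 1.06 SD on a single marker. With baseline adjustment the figure is about 0.92 SD if the baseline correlation is 0.5 (an assumption). If alpha is split over the seven primary markers it is about 1.38 SD without baseline adjustment. The 95% confidence interval for an unadjusted difference has a half-width of about 0.75 SD. Smaller effects cannot be excluded, so a null result is not evidence of no effect.

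The pilot may still be cited as the reason for choosing these markers, but not as a power calculation.

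The cost is wording in two places. No extra participants and no change of design are needed; the price is that the stated sensitivity reads less favourably than the present claim.

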### Assessment of efficacy

### Primary endpoint

Levels of serum inflammatory biomarkers such as; IL-6, IL-10, C-RP, Zonulin (Haptoglobulin), IL-1β, TNFα, IFNᵧ.

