| Description of interventions | Arm A: Pectin fibre (15g/day) combined with 15g whey protein supplement and 5g cocoa powder reconstituted as a shake Arm B (control/placebo): Whey protein supplement (30g/day) and 5g cocoa powder reconstituted as a shake.  To validate MRI scans as a tool to assess intestinal wall thickness to indicate gut permeability on MASLD patients, our team will scan 15 healthy volunteers twice, at baseline and after 6 weeks, and then compare their results with MASLD participant results at baseline and after 6 weeks. |
| Duration of study | Duration of the study:  24 months.  Duration per participant:  Each participant will participate for 6 weeks. |
| Randomisation and blinding | The study will be a parallel design, placebo-controlled, randomised dietary intervention study in which each participant will be randomly assigned to either pectin supplementation or control dietary supplement using online software (sealedenvelope.com). |
| Outcome measures | Primary outcomes:  Quantification of blood markers associated with physiological processes and pathways contributing to systemic inflammation pathway (TNFα, IL-6, IL-10, IFNᵞ, C-Reactive Protein, Zonulin (Haptoglobulin), IL-1β).  Secondary outcomes:   1. Assessment of changes in anthropometric measures 2. Assessment of changes in general metabolic indicators, such as fasting blood glucose and other blood-based markers relevant to MASLD (e.g., CK18-M30, CK18-M65, PROC3, Enhanced Liver Fibrosis (ELF), NIS2+™, YKL-40, microRNA miR-34a-5p, liver-associated enzymes such as Alanine Aminotransferase (ALT), Aspartate Aminotransferase (AST), gamma-glutamyl transferase (GGT), Alkaline Phosphatase (ALP)), bilirubin levels, lipid profiles, and platelet counts. 3. Exploration of modifications in non-invasive physiological assessments linked to liver characteristics, such as fat content and stiffness through controlled attenuation parameter (CAP) and transient elastography. 4. Observation of alteration in fat in liver and other surrounding abdominal organs through Dixon MRI sequence in patients who will agree to have 2 MRI scans. 5. Validation of MRI measures (T2*) as a tool to measure gut permeability among MASLD patients and investigation of changes in gut permeability in participants undergoing two MRI scans. 6. Investigation the presence of gene variants such as MUC2, encoding Mucin protein, that are associated with gut permeability. |

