| Statistical methods | Data input, cleaning and analysis will be conducted using a statistical software such as PRISM or SPSS (IBM Corp, Armonk, New York) or R software (R Foundation for Statistical Computing, Vienna, Austria). Descriptive statistics will be reported as means ± standard deviations (SD) or medians with interquartile ranges (IQR) for continuous variables, and as frequencies and percentages for categorical variables. Prior to analysis, data will be checked for normality using the Shapiro-Wilk test. Standard parametric and non-parametric tests (where assumptions of normality are violated) will be used to assess significance of changes compared to baseline on both pectin arm and placebo arm. Mixed-effects linear regression models will be used to assess the intervention effect of pectin compared to placebo, adjusting for baseline values and relevant covariates such as age, sex, ethnicity and BMI. The interaction between time (baseline and follow-up) and group (pectin vs placebo) will be examined to determine if the changes over time differ between the two groups. P-value < 0.05 will be considered statistically significant for all analyses. |

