## PRIMARY OBJECTIVE

This research aims to study the effects of daily ingestion of LM pectin on inflammation pathways by measuring the blood inflammatory markers associated with physiological processes (TNFα, IL-6, IL-10, IFNᵞ, C - reactive protein, Zonulin (Haptoglobulin), IL-1β).

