### Primary endpoint

Levels of serum inflammatory biomarker such as; IL-6, IL-10, C-RP, Zonulin (Haptoglobulin), IL-1β, TNFα, IFNᵧ.

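### Seven unranked primary markers are each judged at p<0.05 with no adjustment or success rule; if any one counts as success, the false-positive chance is 30% under independence and about 11% even at correlation 0.9

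*Protocol*

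**What the plan says.** Four places in the protocol define what is primary, and all four name the same seven markers.

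- Synopsis, Outcome measures: a closed bracketed list, "TNFα, IL-6, IL-10, IFNᵞ, C-Reactive Protein, Zonulin (Haptoglobulin), IL-1β".
- Primary Objective: the effect of pectin is studied "by measuring the blood inflammatory markers associated with physiological processes", followed by the same closed list.
- Trial / Study Configuration, Primary endpoint: "Levels of serum inflammatory biomarker such as; IL-6, IL-10, C-RP, Zonulin (Haptoglobulin), IL-1β, TNFα" and IFNγ, introduced as examples.
- Assessment of efficacy, Primary endpoint: "Levels of serum inflammatory biomarkers such as; IL-6, IL-10, C-RP, Zonulin (Haptoglobulin", then IL-1β, TNFα and IFNγ, also introduced as examples.

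None of the four ranks one marker above the others. There is no composite, no testing order and no statement of how many markers must be significant.

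The threshold is explicit. The synopsis says "P-value < 0.05 will be considered statistically significant for all analyses", and Statistics, Methods gives 0.05 again directly after its t-test sentence. Neither place says whether the tests are two-sided. The text under Assessment of efficacy says that the change from baseline will be compared between the arms for primary and secondary endpoints alike.

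**The concern.** A reader who asks when this trial would be called positive finds no answer. With seven markers of equal standing and a threshold of 0.05 applied to each, nothing prevents a single p-value below 0.05 from being reported as a positive primary outcome. The error rate of that headline is then not 5% but the chance that at least one of seven tests crosses the line, which is several times larger under most plausible correlations.

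The list is also closed in two places and open in two. Under the open wording an eighth marker could be treated as primary without contradicting the endpoint definition in the Statistics section. Both problems bear on the main conclusion of the trial, and neither can be repaired credibly once the results by arm are known.

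**Working it through.** **Inputs**

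- Number of primary markers: 7, from all four definitions.
- Threshold per test: 0.05, from the synopsis and Statistics, Methods. Two-sided is assumed.
- Sample size: 15 per arm, from Sample size and justification.
- Tests per marker: one is assumed.
- Success rule: not stated. Any one significant marker is assumed to count.
- Correlation between markers: not stated. A common correlation ρ from 0 to 0.9 is assumed.

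The protocol gives no familywise error rate to reproduce. Its only error figure is 0.05 per test, which is also the overall rate if there is exactly one primary test.

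**Step 1. Independent markers.** The chance of at least one false positive is 1 − (1 − 0.05)^7 = 1 − 0.698 = 0.302.

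**Step 2. Correlated markers.** With a common correlation ρ, the seven test statistics share one common factor. Given that factor they are independent, so the rate is 1 − E[P(|Z| < 1.96 given the factor)^7], evaluated numerically. As a check, seven two-sample t-tests with 15 per arm and no true effect were simulated, 40,000 trials for each ρ shown.

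| ρ | Numerical | Simulated t-tests |
| --- | --- | --- |
| 0 | 30.2% | 29.6% |
| 0.3 | 27.1% | 27.5% |
| 0.5 | 23.0% | 23.6% |
| 0.7 | 17.8% | 18.6% |
| 0.8 | 14.9% | 15.1% |
| 0.9 | 11.4% | not run |

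**Step 3. More markers under the open wording.** Eight independent markers give 1 − 0.95^8 = 33.7%; ten give 1 − 0.95^10 = 40.1%.

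**Step 4. After adjustment.** At 0.05/7 = 0.00714 per marker (Bonferroni, which is also Holm's first step), the rate is 1 − (1 − 0.00714)^7 = 4.9% for independent markers and 3.2% at ρ = 0.7. With one named primary marker and one test it is 5.0%.

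**Step 5. Cost in power.** For a two-sided two-sample t-test with 15 per arm:

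| | α = 0.05 | α = 0.00714 |
| --- | --- | --- |
| Difference detectable with 80% power | 1.06 SD | 1.38 SD |
| Power for a true difference of 0.8 SD | 56% | 26% |
| Power for a true difference of 1.0 SD | 75% | 45% |

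Keeping 1.06 SD detectable with 80% power at 0.00714 would take about 25 per arm.

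**The case against.** The strongest reply is that the protocol claims no familywise rate. It sets a threshold per analysis, 0.05 per test is not wrong in itself, and an adjustment is something a separate analysis plan often supplies. The study is also framed as an exploration of mechanism. Part of this stands: it would be wrong to say that the protocol promises 5% overall and fails to deliver it. But the protocol does not leave the matter open. The synopsis applies the unadjusted threshold to every analysis, so a later adjustment would have to overrule it. And if the seven markers are meant as exploratory, calling them primary and judging each as significant at 0.05 does not say so.

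Four stronger readings might be inferred and are not supported.

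- *The primary list is simply open.* It is open in two sections and closed in the synopsis and the Primary Objective. The accurate point is that these disagree.
- *The error rate is 18% to 30%.* The 18% belongs to ρ = 0.7 and is not a floor; at 0.9 the rate is 11%. Every figure also rests on the any-one-counts reading, which the protocol permits but does not state.
- *A chance finding is the likeliest way for this trial to come out positive.* That does not hold in general. If one marker has a true effect, power on it at 15 per arm is 26% for 0.5 SD, 56% for 0.8 SD and 75% for 1.0 SD. The chance of any false positive among the other six is at most about 26% (1 − 0.95^6 = 26.5%, if independent). Above roughly 0.5 SD, the true finding is the likelier one.
- *TNFα is the evident single primary.* Project Rationale says that the earlier study "significantly reduced pro-inflammatory blood markers such as TNFα (p<0.003" and gives IL-10 at p=0.08, but TNFα is offered there as an example. Sample size and justification refers to four significant inflammatory markers in that study and does not name them. The documents do not settle which marker should lead.

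**Conclusion.** The point holds as worded in the heading. That seven unranked markers are primary, and that 0.05 applies to each without adjustment or a success rule, is read directly from the protocol. The size is conditional on one test per marker and on any one significant marker counting as a positive result. Under those conditions the false-positive chance is 30% for independent markers and falls to 11% at a common correlation of 0.9. It stays above 5% throughout that range, so the conclusion does not depend on the unknown correlation, although the exact figure does.

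Counting one test per marker may be generous. Statistics, Methods also names tests of change from baseline, a matched-pair t-test for the group difference and a mixed model, and makes none of them the primary analysis.

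**What to change.** Choose one of two routes before unblinding.

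1. **Keep seven primary markers.** Make the list closed and test it with Holm's procedure at a familywise two-sided 0.05. The cost is the loss of power in step 5, or a larger trial.
2. **Name one primary marker.** The sponsor chooses and justifies it, and tests it at two-sided 0.05. TNFα is one candidate. The other six become secondary or exploratory, with no unadjusted significance claim. The cost is that six markers lose primary status.

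Under either route:

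- Delete *such as* from both Primary endpoint sections, so that they match the synopsis and the Primary Objective. Under route 2, change the primary status of the six markers in all four places.
- Replace the synopsis sentence that sets 0.05 for every analysis, and the 0.05 sentence in Statistics, Methods, with the chosen rule.
- Designate the between-arm, baseline-adjusted model already described in Statistics, Methods as the single primary test for each marker. Without this, neither route secures 5%, because several tests per marker would remain available.

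These are wording changes. They need no new visits, samples or measurements.
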